#### Study population

The *inclusion criteria* are as follows:Participants with normoalbuminuria (uACR < 30 mg/g) who complete Aim 1 are eligible for Aim 2 (Fig. 1).Participants that completed Aim 1 of the separate, ongoing R3 study [13, 14] having normoalbuminuria (uACR < 30 mg/g) based on the average of two previously obtained uACR measurements (4–8 weeks apart) and re-confirmed via an additional uACR measurement obtained at time of screening for this study are also eligible.

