#### Study measures

##### Urine albumin-to-creatinine ratio (uACR)

*In* the Aim 1 cross-sectional arm, we will determine an average uACR (based on 2 uACR measurement values obtained 4–8 weeks apart) for the 500 newly enrolled HIV-positive, ART-treated adults (on ART < 24 months) plus the 750 age- and sex-matched HIV-negative controls. We will obtain one confirmatory uACR from the 2000 HIV-positive, ART-treated adults that we will call back from the R3 Study; all these participants have two uACR measurements from the R3 screening phase.

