Procedure / Visit (month (mo))	Enrollment	6 mo	12 mo	24 mo	30 mo
Seated blood pressure check	X	X	X	X	X
Diabetes mellitus screening (perform fasting blood glucose if any signs/symptoms suggestive of underlying diabetes)	X^*^	X	X	X	X
uACR^a^ (No urine protein testing necessary for enrolled Aim 2 HIV-positive adults with normoalbuminuria as all HIV-positive ART-treated adults from Aim 1 will have one uAPR measurement) (We will have stored urine at 3 timepoints to go back and perform uAPR testing in patients with incident microalbuminuria)	X^#^ (We will use Aim 1 uACR as participants baseline value)		X		X
Serum creatinine (SCr)^b^	X (We will use Aim 1 SCr as their baseline value)		X		X
Parasite screening					
Complete blood count (CBC) with differential^c^	X	X	X	X	X
Urine dipstick (spun for all patients with hematuria followed by urine microscopy (*S. haematobium*)	X	X	X	X	X
Malaria testing (rapid diagnostic test) at point-of-care (POC) using fingerprick specimen	X	X	X	X	X
Filariasis POC testing for *Wuchereria bancrofti*^d^	X				X
Onchocerciasis testing (bilateral skin snips)^e^	X				X
Stool for ova and parasite (stool O&P)^f^	X	X	X	X	X
Daytime thick blood smear for *Loa loa* (10 AM–2 PM)	X				X
Strongyloides IgG serology (plasma)^g^	X				X
Tuberculosis screening^h^	X	X	X	X	X
Inflammatory biomarkers (urine and plasma)^i^	X				X
CD4 cell count	X				X
Viral load (plasma HIV RNA)	X				X
Social and Behavioral data	X		X		X
Additional tubes for storage^j^	X		X		X

*All potentially eligible Aim 2 participants will undergo fasting blood glucose testing to evaluate for diabetes (and if ≥ 6.1

mmol/L (110 mg/dL), then patient may have diabetes, is ineligible, and is referred to medical provider/clinic for evaluation

^#^All participants will use their recent uACR measurement (obtained in Aim 1) for their baseline

^a^Two 3 mL sterile universal containers taken for uACR testing (Urine protein testing only for HIV-positives)

^b^Two 3 mL gold top tubes taken to measure serum creatinine (SCr)

^c^CBC with differential—looking for eosinophilia (common with Filariasis (especially *Loa loa*) and Schistosomiasis)

^d^POC testing for *W. bancrofti* antigen by Filariasis Test Strip (FTS), followed by obtaining nocturnal thick blood smears for

microfilaria [between 10 pm—2 am] in FTS-positive persons. *Brugia spp. *are not endemic to Africa, so testing for *W*

*bancrofti* will be sufficient

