^e^*Onchocerca volvulus *ELISA is not sensitive enough to rule out infection. Physical exam findings are also not sensitive. No one

will want to be snipped every 6 months, but since filarial worms are long-lived (> 5 years), snipping at the beginning and end

of study should capture anyone who is infected at study onset or becomes infected during the study

^f^Stool for O&P to be done screening for *S. mansoni* and soil transmitted helminths (e.g., Ascaris, Trichuris, Hookworm)

^g^Strongyloides IgG ELISA at baseline in ALL participants & test all persons testing NEG at enrolment again at 30 months

^h^Sputum specimens (5 mL) to be collected and sent for Gene Xpert testing and/or microscopy (acid fast bacilli staining)

^i^Two 3 mL purple top tubes for plasma biomarkers and one 5–7 mL urine specimens for urine biomarkers (and stored)

^j^Two 3 mL purple top EDTA tubes and one 5–7 mL urine specimen to be obtained and stored for future/approved testing

*Clinical Assessments* at all comprehensive study visits will be performed by trained study nurses and will include:*Vital signs:* temperature, respiratory rate, heart rate, blood pressure (Seated BP checked every study visit using a validated Omron series 5 upper arm digital BP device).*Anthropometrics*: height, weight, waist circumference*Urine albumin testing*, *uACR measurements*: Albuminuria will be assessed at each visit and categorized as defined in Aim 1. Subjects with incident macroalbuminuria will be referred to a clinician for evaluation and to a nephrologist for additional testing/management, per standard of care.*Urine albumin-to-protein [uAPR] ratios (HIV-positive participants)*: will be assessed to screen for possible TDF-mediated tubular insult as a contributing cause of microalbuminuria. Subjects with *uAPR* < *40%* will be classified as *tubular albuminuria* and those with *uAPR* ≥ *40%* will be classified as *glomerular albuminuria*.*Diabetes screening*: All potentially eligible Aim 2 participants will undergo fasting/random blood glucose testing to evaluate for diabetes (and if ≥ 6.1 mmol/L (110 mg/dL), then patient may have diabetes, is ineligible, and is referred to medical provider/clinic for evaluation. Once enrolled, during each study visit, participants will be screened for symptoms of diabetes. In those with symptoms, we will perform fasting/random blood glucose testing. if ≥ 6.1 mmol/L (110 mg/dL), they will be immediately referred to a specialist for further evaluation.

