#### Statistical analysis plan

Demographic and clinical characteristics will be summarized by descriptive statistics. We will perform two sets of analyses: (1) categorizing uACR and investigating time from enrollment to albuminuria onset (first uACR measurement > 30 mg/g), and (2) keeping uACR as a continuous variable and investigating mean change in repeated uACR measures. Categorization of uACR is common in the literature and allows easy clinical interpretation, whereas continuous analysis tends to result in greater power. For (1), discrete-time proportional hazards models with a complementary log–log link will be fit. For (2), generalized estimating equations (GEE) with an identity link (i.e., linear model) will be fit to repeated measures of log_10_-transformed uACR. We will fit models limited to PWH, with cumulative TDF exposure as the primary (time-varying) exposure. The association between albuminuria and cumulative exposure to other regimens (e.g., protease inhibitors) will also be considered, both in models with and without cumulative TDF exposure. Analyses will adjust for viral suppression status. Secondary analyses will exclude the anticipated small proportion (< 5%) that will not be virally suppressed.

For hypothesis (ii), we will fit models with HIV status, hypertension, and an interaction between HIV status and hypertension. For hypothesis (iii), we will fit models with time-updated biomarkers of inflammation, both current and cumulative exposure. For inflammatory analyses, we will compute a composite inflammation score [102] for each participant that has been shown to accurately predict the phenotype of interest, based on levels (at least initially) of select markers, with a score of 1 being assigned to each individual biomarker measurement deemed “*high*” (or “*significantly elevated*”) delineated as follows: hsCRP > 3 mg/L, IL-6 > 6 pg/mL, TNF ≥ 7 pg/mL, and IL-1β ≥ 0.39 pg/mL. We will also perform analyses including inflammation biomarkers as continuous variables, both individually and in combination with other biomarkers.

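### Aim 2 screens R3 participants more strictly than HIV-negative adults and calls onset on one unconfirmed uACR, so measurement noise enters the HIV incidence contrast by an amount and in a direction the plan does not fix

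*Protocol article*

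**What the plan says.** The Aim 2 Study population section gives two ways in. The general route reads "Participants with normoalbuminuria (uACR < 30 mg/g) who complete Aim 1 are eligible for Aim 2". For the 500 newly enrolled PWH and the 750 HIV-negative adults, the Aim 1 uACR section defines the value: "we will determine an average uACR (based on 2 uACR measurement values obtained 4–8 weeks apart". The R3 route needs an average below 30 from the earlier pair, "re-confirmed via an additional uACR measurement obtained at time of screening for this study are also eligible". The same Aim 1 section confirms that R3 entrants carry three readings: one new one, and "all these participants have two uACR measurements from the R3 screening phase".

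The Aim 2 Statistical analysis plan defines the event through "time from enrollment to albuminuria onset (first uACR measurement > 30 mg/g", with no confirming sample. The footnote to Table 6 sets the baseline: "All participants will use their recent uACR measurement (obtained in Aim 1) for their baseline". That is one recall reading for R3 entrants and a two-reading average for everyone else.

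The confounders named in that analysis plan do not include baseline uACR, entry route or the number of qualifying readings. Table 6 marks follow-up uACR at months 12 and 30 only, while the clinical assessments text says "Albuminuria will be assessed at each visit and categorized as defined in Aim 1".

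**The concern.** A person whose usual uACR lies just under 30 mg/g can cross the threshold on a later sample with no change in the kidney. Each further qualifying reading removes some of these people at entry. Every HIV-negative adult enters after two readings. Most PWH enter after three, and the third must itself be below 30. With a single-sample event, the less-screened group then shows more false onset at any given uACR distribution. Entry route is tied to HIV status, the exposure compared in Table 7, so this does not cancel out.

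The change analysis is affected in another way. For R3 entrants the baseline is one reading chosen for being below 30, so later readings drift up on average. The others start from an average of two.

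**Working it through.** **Plan's own figure.** Table 7, bold row: 10% of 1000 against 5.9% of 500. Arcsine formula: h = 2(arcsin√0.10 − arcsin√0.059) = 2(0.3218 − 0.2454) = 0.153. Multiplying by √(1000×500/1500) = 18.26 gives 2.79, and 2.79 − 1.96 = 0.83, so power is 79.7%. The stated 80% reproduces. The planned difference is 10 − 5.9 = 4.1 points.

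**Share of PWH from R3.** The article does not state it. The Aim 1 sample size section assumes the 500 new PWH share the roughly 40% prevalence, so at most about 500 × 0.60 = 300 qualify. At least 1000 − 300 = 700, or 70%, then come from R3.

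**Noise-only onset.** Simulation of 2 million persons per setting:
- log10 uACR has mean 1.35 and SD 0.554 (Aim 1 sample size section), taken as the SD of a two-reading mean. It is first set equal in both groups, with no true change.
- Entry is an arithmetic mean of two readings below 30, with or without a third reading below 30.
- Onset is either of two later readings (months 12 and 30) above 30.
- Within-person SD of log10 uACR is not in the article; 0.10 to 0.30 is assumed.
- With 70% from R3, the HIV-group gap is I_two − (0.7·I_R3 + 0.3·I_two) = 0.7 × (I_two − I_R3).

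| Assumed SD | Two-reading entry | R3 entry | Route gap (points) | Gap between HIV groups, 70% R3 |
|---|---|---|---|---|
| 0.10 | 8.9% | 5.9% | 3.0 | 2.1 |
| 0.15 | 13.1% | 9.0% | 4.1 | 2.9 |
| 0.20 | 17.4% | 12.4% | 5.0 | 3.5 |
| 0.25 | 21.6% | 15.9% | 5.7 | 4.0 |
| 0.30 | 25.8% | 19.6% | 6.2 | 4.3 |

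If true levels drifted between R3 screening and recall (correlation 0.8, assumed), the route gap is 2.2 to 4.4 points, or 1.5 to 3.1 at 70% R3.

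**Lower uACR in HIV-negative adults.** HIV-negative minus PWH, in points, over SD 0.10 to 0.30 unless stated:
- Prevalence 33.6% (Table 3): about +1.6 to +2.7 if all PWH are from R3; +0.7 to +1.0 at 70%.
- log10 mean 1.28 (the continuous detectable value): about +1.2 to +2.1 at 70% (SD 0.10 to 0.35).
- Bold row of Table 5 with 10% hypertensive, 0.9×0.25 + 0.1×0.50 = 27.5%: about −0.1 to +0.6 if all are from R3; −0.4 to −2.0 at 70%.
- Top row of Table 5, 0.9×0.10 + 0.1×0.27 = 11.7%: about −2.7 to −9.1 if all are from R3; −3.6 to −10.9 at 70%.

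Two effects are mixed here. At the Table 3 value with all PWH from R3, subtracting the route gap leaves 1.6 − 3.0 = −1.4 points (SD 0.10) and 2.7 − 6.2 = −3.5 (SD 0.30). That remainder comes from the lower uACR level and would persist under a common two-reading rule. It is somewhat smaller under a common three-reading rule.

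**Confirmed onset.** Requiring a repeat also above 30 cuts noise-only onset to 3.8–10.7% (two-reading entry) and 1.9–6.4% (R3 entry). A gap of 3.8 − 1.9 = 1.9 to 10.7 − 6.4 = 4.3 points remains, so confirmation alone does not equalise the routes.

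**Change in log10 uACR.** With no true change, R3 entrants show about +0.006 to +0.06. Two-reading entrants show about 0 to +0.015 when baseline is the log10 of the arithmetic average. Averaging the two log10 values instead brings the two routes close together, so the kind of baseline matters as well as the selection.

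**The case against.** The strongest reply is that the plan itself expects lower uACR in HIV-negative adults, so a simulation with equal distributions is not the study's own scenario. This stands. A reader might infer that noise produces a gap as large as the planned difference, or that it must mask an HIV effect. The article supports neither inference: at the Table 3 value the shift is well below 4.1 points, and over much of the Table 5 range the net noise excess lies with PWH.

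A reader might also add noise events to both planned rates: with 8.9% noise-only onset in each group, 10% against 5.9% becomes 18.0% against 14.3%, a relative risk of 1.26 with power of about 44%. This is not established. Table 7 does not say that its rates exclude single-sample crossings. The simulation also gives up to about 26% false onset against planned incidence of 5 to 15% in PWH, so its upper settings may not fit this population.

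Nor does Aim 1 require both samples to exceed 30; it averages them. The case for confirming onset rests on noise, not on an Aim 1 rule.

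The R3 re-check has a sound reason: the earlier pair is old, and current status is needed. That justifies the check but not its absence elsewhere. New PWH skip it too, which dilutes the HIV-group gap, as the 70% column shows.

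Finally, the Aim 2 hypotheses concern hypertension, inflammation and TDF, and the sizes above address only the HIV contrast. Within PWH, however, entry route also goes with time on ART, so the TDF analysis is not clearly free of the problem. No size was worked out for it.

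**Conclusion.** The concern holds in a limited form. Eligibility, baseline and event definition are fixed in the article, and they make misclassified onset depend on entry route, which is strongly tied to HIV status. At a given uACR distribution the two-reading route yields about 3 to 6 points more noise-only onset, or about 2 to 4 points in the HIV contrast if 70% of PWH are from R3. The net shift falls to about 1 to 2 points at the Aim 1 planning values and may reverse at Table 5 prevalences. R3 log10 change is biased upward by about 0.006 to 0.06.

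These sizes rest on an assumed within-person SD, an inferred R3 share and two follow-up readings. None of the listed adjustments corrects for entry route. The point deserves a change to the plan, but it does not show that the HIV comparison will fail.

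**What to change.** 1. Assay uACR on the Aim 2 enrolment urine from those without a current single reading, apply the same below-30 rule to all groups, and use the same kind of baseline value for everyone. Table 6 already collects and stores this urine, so the rule could also be applied later as a restriction of the analysis set. Cost: about 500 + 300 = 800 assays, and roughly 5 to 15% of two-reading entrants no longer qualify.
2. Add analyses that need no new samples:
   - Count month-12 onset only if month 30 is also above 30. Report first crossings at month 30 separately, since the schedule cannot confirm them.
   - Adjust for baseline uACR and entry route.
   - Compare HIV-negative adults with newly enrolled PWH only, stating the lower precision. At the planned rates the 95% half-width is 1.96×√(0.09/300 + 0.0555/500) = 4.0 points, against 1.96×√(0.09/1000 + 0.0555/500) = 2.8 for the full comparison.
3. Reconcile Table 6 (months 12 and 30) with the text that assesses albuminuria at every visit, because more readings mean more chance crossings.

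Equal entry removes only the route-driven part. Noise differences from different underlying uACR levels remain; the persistence requirement reduces them, so both steps are needed.

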#### Exclusion criteria

Did not complete all scheduled Aim 1 visitsPregnancy (all women with reproductive potential will undergo urine pregnancy testing)Diabetes mellitus (documented diagnosis or random glucose ≥ 6.1 mmol/L [110 mg/dL])Known congenital kidney disease and/or autoimmune disease that can cause albuminuriaActively taking ACEi or ARBs, which may suppress albuminuriaRegular use of NSAIDs or traditional medicationsHIV-negative but use TDF as pre-exposure prophylaxis or HBV treatmentComorbid condition with life expectancy < 3 yearsPlanning to relocate within three years

#### Study procedures

Whole blood and urine biospecimens will be obtained for processing for plasma and urine pellets which will be processed and shipped to their respective research laboratories, namely, Duke University (plasma biomarker, *Cytomegalovirus* (CMV) IgG antibody (Ab) testing, and *APOL1* genotyping) and Brigham and Women’s Hospital (urine biomarkers and urine albumin, creatinine, and protein testing). Participants will receive reimbursement for comprehensive study visits. All HIV-negative study participants will be asked to complete a brief risk assessment at each study visit, with reflex viral load testing in those deemed high risk, as outlined in Aim 1 (study procedures). If their HIV test results are positive, they will no longer participate in longitudinal follow-up. Data collected prior to seroconversion will be maintained. Longitudinal assessments (enrollment visit and then every 6 months for 30 months for a total of 5 scheduled visits for each participant) will include the following (*as outlined below*):

#### Study measures

*Demographic and clinical data elements* will be abstracted from medical record and by self-report at baseline and will be updated during every scheduled study visit.*Demographics*: age, sex, self-reported ethnicity (Hausa/Fulani, Igbo, Yoruba, Other (Specify)*Education*: not literate, primary, secondary, tertiary (university or other college).*Occupation*: employment status (and if employed; details to be obtained)*HIV transmission risk factors*: heterosexual activity, homosexual activity, transfusion, other, unknown*Date of HIV diagnosis (PWH only)*: date of first positive HIV test*Date of ART initiation (PWH only)*: defined as three or more active antiretrovirals from two or more drug classes*Dates of AIDS-defining illnesses (PWH only)*: defined per CDC list of AIDS-defining illnesses*Dates of comorbid disease diagnoses*: infections including TB (pulmonary and extrapulmonary), viral infections (HBV, HCV [Aim 1], Lassa fever, COVID-19, etc.), AIDS-defining illnesses; NCDs including hypertension, diabetes, sickle cell trait or disease, dyslipidemia, cardiovascular disease, cancer, liver disease, lung disease, depression, and bone mineral density abnormalities (including non-traumatic fractures).*Antiretroviral medication start/stop dates (PWH only)*: from clinical record and pharmacy data (evaluating current exposure as well as prior/current TDF, protease inhibitor use to determine cumulative exposure time).*Current medications*: all medications taken at least once daily for ≥ 30 days, including traditional medications.*Laboratory HIV data*: all CD4 cell count and viral load measurements (collected per standard of care)**.** SARS-CoV-2 testing will be performed per existing standard of care and results of all COVID-19 screening tests will be captured in the patients’ study medical record).

*Social and behavioral data* will be collected three times during study follow-up using the following scales, which are all available in both English and Hausa languages (Table 6).*Substance use:* The Alcohol, Smoking and Substance Involvement Screening Test (ASSIST) is a cross-cultural screening of recent and lifetime substance use [90].*Depression:* The 9-item Patient Health Questionnaire (PHQ-9) [91] screens for depressive symptoms.

**Table 6 Tab6:** Procedures for longitudinal cohort of HIV-positive (n = 1,000) and HIV-negative (n = 500) participants with normoalbuminuria to be followed for 30 months (n = 1500 total)

Procedure / Visit (month (mo))	Enrollment	6 mo	12 mo	24 mo	30 mo
Seated blood pressure check	X	X	X	X	X
Diabetes mellitus screening (perform fasting blood glucose if any signs/symptoms suggestive of underlying diabetes)	X^*^	X	X	X	X
uACR^a^ (No urine protein testing necessary for enrolled Aim 2 HIV-positive adults with normoalbuminuria as all HIV-positive ART-treated adults from Aim 1 will have one uAPR measurement) (We will have stored urine at 3 timepoints to go back and perform uAPR testing in patients with incident microalbuminuria)	X^#^ (We will use Aim 1 uACR as participants baseline value)		X		X
Serum creatinine (SCr)^b^	X (We will use Aim 1 SCr as their baseline value)		X		X
Parasite screening					
Complete blood count (CBC) with differential^c^	X	X	X	X	X
Urine dipstick (spun for all patients with hematuria followed by urine microscopy (*S. haematobium*)	X	X	X	X	X
Malaria testing (rapid diagnostic test) at point-of-care (POC) using fingerprick specimen	X	X	X	X	X
Filariasis POC testing for *Wuchereria bancrofti*^d^	X				X
Onchocerciasis testing (bilateral skin snips)^e^	X				X
Stool for ova and parasite (stool O&P)^f^	X	X	X	X	X
Daytime thick blood smear for *Loa loa* (10 AM–2 PM)	X				X
Strongyloides IgG serology (plasma)^g^	X				X
Tuberculosis screening^h^	X	X	X	X	X
Inflammatory biomarkers (urine and plasma)^i^	X				X
CD4 cell count	X				X
Viral load (plasma HIV RNA)	X				X
Social and Behavioral data	X		X		X
Additional tubes for storage^j^	X		X		X

*All potentially eligible Aim 2 participants will undergo fasting blood glucose testing to evaluate for diabetes (and if ≥ 6.1

mmol/L (110 mg/dL), then patient may have diabetes, is ineligible, and is referred to medical provider/clinic for evaluation

^#^All participants will use their recent uACR measurement (obtained in Aim 1) for their baseline

^a^Two 3 mL sterile universal containers taken for uACR testing (Urine protein testing only for HIV-positives)

^b^Two 3 mL gold top tubes taken to measure serum creatinine (SCr)

^c^CBC with differential—looking for eosinophilia (common with Filariasis (especially *Loa loa*) and Schistosomiasis)

^d^POC testing for *W. bancrofti* antigen by Filariasis Test Strip (FTS), followed by obtaining nocturnal thick blood smears for

microfilaria [between 10 pm—2 am] in FTS-positive persons. *Brugia spp. *are not endemic to Africa, so testing for *W*

*bancrofti* will be sufficient

^e^*Onchocerca volvulus *ELISA is not sensitive enough to rule out infection. Physical exam findings are also not sensitive. No one

will want to be snipped every 6 months, but since filarial worms are long-lived (> 5 years), snipping at the beginning and end

of study should capture anyone who is infected at study onset or becomes infected during the study

^f^Stool for O&P to be done screening for *S. mansoni* and soil transmitted helminths (e.g., Ascaris, Trichuris, Hookworm)

^g^Strongyloides IgG ELISA at baseline in ALL participants & test all persons testing NEG at enrolment again at 30 months

^h^Sputum specimens (5 mL) to be collected and sent for Gene Xpert testing and/or microscopy (acid fast bacilli staining)

^i^Two 3 mL purple top tubes for plasma biomarkers and one 5–7 mL urine specimens for urine biomarkers (and stored)

^j^Two 3 mL purple top EDTA tubes and one 5–7 mL urine specimen to be obtained and stored for future/approved testing

*Clinical Assessments* at all comprehensive study visits will be performed by trained study nurses and will include:*Vital signs:* temperature, respiratory rate, heart rate, blood pressure (Seated BP checked every study visit using a validated Omron series 5 upper arm digital BP device).*Anthropometrics*: height, weight, waist circumference*Urine albumin testing*, *uACR measurements*: Albuminuria will be assessed at each visit and categorized as defined in Aim 1. Subjects with incident macroalbuminuria will be referred to a clinician for evaluation and to a nephrologist for additional testing/management, per standard of care.*Urine albumin-to-protein [uAPR] ratios (HIV-positive participants)*: will be assessed to screen for possible TDF-mediated tubular insult as a contributing cause of microalbuminuria. Subjects with *uAPR* < *40%* will be classified as *tubular albuminuria* and those with *uAPR* ≥ *40%* will be classified as *glomerular albuminuria*.*Diabetes screening*: All potentially eligible Aim 2 participants will undergo fasting/random blood glucose testing to evaluate for diabetes (and if ≥ 6.1 mmol/L (110 mg/dL), then patient may have diabetes, is ineligible, and is referred to medical provider/clinic for evaluation. Once enrolled, during each study visit, participants will be screened for symptoms of diabetes. In those with symptoms, we will perform fasting/random blood glucose testing. if ≥ 6.1 mmol/L (110 mg/dL), they will be immediately referred to a specialist for further evaluation.

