Visit specifics are outlined in Table 1 (see above) for the newly enrolled 1250 study participants (500 HIV-positive adults on ART < 24 months plus the age- and sex-matched 750 HIV-negative adults) and in Table 2 (see below) for the 2,000 R3 participants that will be called back. Cross-sectional study visits will be completed by 1250 total participants, including 500 HIV-positive, ART-treated adults (18–69 years of age) on ART for < 24 months, plus 750 age- and sex-matched HIV-negative adults (Fig. 1). We will measure urinary albumin and creatinine levels to calculate a mean (two-sample) uACR. In the 500 HIV-positive adults, we will also measure urine protein (once at Visit 1) to perform a urine albumin-to-protein ratio (uAPR). In addition, we will call back R3 participants who completed screening but were not enrolled in the randomized trial for additional measurements. We anticipate obtaining these additional measurements from ~ 2000 R3 participants (conservatively assuming 90% re-consent). In participants called back from R3, we will obtain one uACR measurement (to confirm their current albuminuria status), one uAPR measurement (to evaluate the potential impact of current/prior TDF exposure), and serum creatinine. We will leverage archived specimens for HBV and CMV serology testing. HCV antibody testing will be performed if we identify a higher-than-expected prevalence in a random sample of 200 PWH.

**Table 2 Tab2:** Procedures for one time cross-sectional study visit for the HIV-positive, ART-treated adults that participated in the Renal Risk Reduction (R3) study and now called back (n = 2,000)

Visit 1	
-Screening, informed consent -Blood pressure measurement -Diabetes screening^a^ -Enrollment (if meet eligibility criteria) -Participant to provide urine specimen at study clinic on day of visit (for uACR and uAPR)	-Participant to provide urine specimen at study clinic on day of visit (for one-time uACR and uAPR) **Specimen collection** (~ 3 tubes; ~ 15 mLs total) i) *Serum creatinine* (3 mL gold top tube) ii) *HBV*^*b*^* and HCV testing*^c^ (leverage existing stored plasma aliquots) iii) *CMV testing*^d^ (leverage existing stored plasma aliquots) iv) *Additional specimens to store* (Two urine aliquots: Two 3 mL EDTA tubes; toenail/hair samples from consenting patients)

^a^Screen for diabetes (if symptomatic, e.g., polyuria, polydipsia, weight loss), perform fasting/random glucose test (point-of-

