#### Study outcomes

Proportion of Aim 2 longitudinal cohort participants experiencing progression from normoalbuminuria (uACR < 30 mg/g) to microalbuminuria (uACR = 30–300 mg/g), at 30 months of follow-up, overall, and by TB infection, parasitic infection, and inflammation (high levels of plasma and/or urine inflammatory marker levels) status.Proportion experiencing a doubling of serum creatinine.Proportion experiencing a decline in eGFR > 30% at 30 months (using the 2021 CKD-EPI eGFR creatinine (age and sex)) equation.Mean change in eGFR at 30 months (using the 2021 CKD-EPI eGFR creatinine (age and sex)) equation.Mean change in uACR at 30 months.

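### The Aim 2 baseline uACR is a two-reading arithmetic mean for some participants and a single reading for R3 participants, which biases group comparisons of log10 change

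*Protocol article*

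**What the plan says.** - **Aim 2 baseline.** In Table 6 (Specific aim 2, Study measures) the enrolment cell of the uACR row reads "We will use Aim 1 uACR as participants baseline value". Footnote # repeats it for everyone: "All participants will use their recent uACR measurement (obtained in Aim 1) for their baseline".
- **What that value is for new participants.** Specific aim 1, Study measures, says of the 500 newly enrolled PWH and the 750 HIV-negative adults: "we will determine an average uACR (based on 2 uACR measurement values obtained 4–8 weeks apart". The Aim 1 study procedures add: "We will measure urinary albumin and creatinine levels to calculate a mean (two-sample) uACR". Neither place mentions a log-scale or geometric mean.
- **What it is for R3 participants.** "We will obtain one confirmatory uACR from the 2000 HIV-positive, ART-treated adults that we will call back from the R3 Study". Their two older R3 readings count towards Aim 2 eligibility, and those who are also "re-confirmed via an additional uACR measurement obtained at time of screening for this study are also eligible".
- **Follow-up.** Table 6 schedules uACR at months 12 and 30. Its footnote a lists two urine containers but states no averaging.
- **Analysis.** The Aim 2 outcomes include "Mean change in uACR at 30 months". In the Aim 2 statistical analysis plan, "generalized estimating equations (GEE) with an identity link (i.e., linear model) will be fit to repeated measures of log_10_-transformed uACR". That section expects the continuous analysis to have more power than the categorised one.

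**The concern.** The number of readings behind the baseline depends on how a participant was recruited, and recruitment route goes with HIV status. Every HIV-negative adult has a two-reading mean, while most PWH in Aim 2 have one reading. The values are averaged in mg/g and analysed on log10, so the two kinds of baseline are not on the same footing. A two-reading baseline sits too high against later readings of the same person, which makes that person's log10 change look smaller.

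At stake is any comparison of log10 change between PWH and HIV-negative adults. The models limited to PWH may be touched as well. New recruits have at most about 24 months of ART, whereas R3 participants were ART-experienced and mostly had some TDF exposure. Baseline type therefore tracks ART duration, and probably cumulative TDF exposure, which is the primary exposure in those models.

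**Working it through.** **Plan's own figure first.** The article gives no power figure for the Aim 2 change analysis. The nearest is Aim 1: about 90% power for 0.132 SD with 750 and 3000 participants. SE = √(1/750 + 1/3000) = 0.0408 SD; 0.132/0.0408 = 3.23; power = Φ(3.23 − 1.96) = 0.90. It reproduces. On the log10 scale it is 0.132 × 0.554 = 0.073, a useful yardstick below.

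**Inputs from the article.** Log10 uACR mean 1.35 and SD 0.554; entry below 30 mg/g; 1000 PWH and 500 HIV-negative adults; two-sided 5% as in Aim 1.

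**Assumed inputs.**
- Within-person SD of log10 uACR, s: not given; 0.15 to 0.35 tried.
- R3 share of PWH: with about 40% albuminuria in new recruits, as the article assumes, at most 500 × 0.60 = 300 can enter, so 700 of 1000 (70%) come from R3.

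**Mechanism.** For two readings with normal errors on log10, the mean lift of log10(arithmetic mean) over the mean of the logs is approximately ln(10) × s²/4. At s = 0.20 this is 2.303 × 0.04/4 = 0.023; at s = 0.30 it is 2.303 × 0.09/4 = 0.052. For one pair, 8 and 22 mg/g: log10(15) = 1.176, mean of the logs 1.123, lift 0.053.

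**Null simulation.** No one changes, and both HIV groups share one distribution. Controls and new PWH enter if their two-reading mean is below 30, and that mean is the baseline. R3 PWH need the same from two earlier readings plus a third reading below 30, and the third is the baseline. Follow-up is one reading. The gap for all PWH is 0.7 × (R3 change − two-reading change), because new PWH have the same kind of baseline as controls. Rejection is Φ(gap/SE − 1.96) plus the negligible opposite tail, with the SE for 1000 against 500.

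| s | Change, R3 | Change, two-reading baseline | Difference | Gap, 70% R3 | SE | Rejection |
|---|---|---|---|---|---|---|
| 0.15 | +0.0145 | +0.0015 | 0.0129 | 0.009 | 0.0105 | 14% |
| 0.20 | +0.0269 | +0.0046 | 0.0223 | 0.016 | 0.0140 | 20% |
| 0.25 | +0.0436 | +0.0096 | 0.0340 | 0.024 | 0.0174 | 28% |
| 0.30 | +0.0663 | +0.0193 | 0.0470 | 0.033 | 0.0207 | 36% |
| 0.35 | +0.0955 | +0.0339 | 0.0616 | 0.043 | 0.0239 | 44% |

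The gap is 2% to 10% in uACR (10^0.009 = 1.02; 10^0.043 = 1.10), or 12% to 59% of the 0.073 yardstick. Both groups drift upwards because both were selected below 30 mg/g; only the difference is the artefact. A different number of follow-up readings, if the same in both groups, would change both columns almost equally.

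**Sensitivity to the analysis and to the reading of the footnote.**
- Baseline as a covariate instead of subtracted: HIV coefficient about 0.006 to 0.012, rejection about 6% to 10%.
- Visit 2 reading alone as the baseline of new participants: R3-minus-control difference 0.0006 to 0.0084, so at most 0.7 × 0.0084 = 0.006 for all PWH.
- Mean of the two log10 readings: the same to within 0.0002, with rejection of 5% to 6%.

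The last line shows that the averaging scale, not the differing entry rules, produces nearly all of the gap.

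**Within PWH.** The R3-minus-new difference is the undiluted fourth column, 0.013 to 0.062. How much of it would pass into a TDF coefficient depends on the exposure distribution, which the article does not give.

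**The case against.** The strongest reply is that the article does not specify the test simulated above. The Aim 2 statistical analysis plan names no HIV-by-time term and does not say whether baseline is an outcome row, a covariate or a value to subtract. The result depends on that choice: with baseline as a covariate, most of the excess rejection goes. An HIV main effect averaged over all visits would even place PWH lower than controls (by about 0.03 to 0.065 log10 in a simulation under the same assumptions), through the extra R3 entry confirmation together with the lifted control baseline. This stands. A reader might infer that a planned test has a false-positive rate well above 5%; the document does not support that.

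A reader might also infer that the bias favours the study's own hypothesis. It does not follow. The Aim 2 hypotheses concern hypertension, inflammation and cumulative TDF among PWH; none predicts a faster uACR rise in PWH. The HIV contrast powered in Table 7 is for incidence.

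Nor should the pair 8 and 22 be read as showing that controls will appear to fall. It illustrates the lift only. It implies a within-person SD near 0.31 and ignores the entry rule, under which both groups rise.

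Finally, footnote # speaks of a measurement in the singular, and averaging before or after logs is a detail that a condensed article may leave to the full plan. The first point is fair: read as Visit 2 only, the footnote nearly removes the problem. But Aim 1 defines these participants' uACR as the two-reading mean, and the Table 6 cell carries the Aim 1 uACR forward. The second point is weaker, because the article does state a derivation rule, and that rule, taken with the log10 analysis, gives unequal baselines.

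**Conclusion.** The point holds as a bias in a comparison that the design supports. On the natural reading of Table 6, the baseline differs in kind between R3 PWH and everyone else, and a comparison of log10 change by HIV status is shifted towards a larger rise in PWH with no true change. The sign was positive at every within-person SD tried. The size, about 0.009 to 0.043 log10 with 14% to 44% null rejection, is conditional on a change-score analysis, 70% of PWH from R3 and an assumed within-person SD of 0.15 to 0.35. It is not a proven error rate of a named primary test. PWH-only change models may inherit the artefact through ART duration, by an amount that cannot be computed here. The log-of-a-mean lift does not arise for change in untransformed mg/g, and time to albuminuria is a separate matter.

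**What to change.** In Table 6 footnote # and in the Aim 2 statistical analysis plan, state that analyses of log10 uACR take as baseline the mean of the log10 values of the individual Aim 1 readings. Alternatively, enter each Aim 1 reading as its own baseline record in the GEE. Apply the same rule in both HIV groups and to R3 and new PWH alike, and do not take log10 of the averaged uACR. State also whether the baseline is an outcome record, a covariate or subtracted.

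The cost is wording only, since the individual readings are already collected. A residual gap of about 0.005 to 0.006 log10 at most, over the same range of within-person SD, remains from the differing entry rules.
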